### 2.2. Outcomes

The primary outcome will be noninferiority of the cure rate of immunosuppressed patients compared to immunocompetent patients. Cure rate is defined as the proportion of patients with a negative direct parasitological test and negative *S. stercoralis* serology or decrease of at least 50% of OD index at 6 months after treatment administration. We used a noninferiority margin of 14% to assess the primary outcome (i.e., lower bound of the 1-sided 95% CI of the difference between cure rates in immunosuppressed versus immunocompetent patients was no more than –14%). The secondary objective will be to compare the safety and tolerability of single dose ivermectin for the treatment of uncomplicated strongyloidiasis between immunosuppressed and immunocompetent patients. Three sub-studies have been prespecified: Evaluation of the usefulness of *S. stercoralis* PCR in feces in the follow-up after treatment of uncomplicated strongyloidiasis in adult patients (proportion of patients with negative *S. stercoralis* PCR after treatment compared to proportion of patients that fulfill the cure criteria),Determination of the population pharmacokinetics (PK) of ivermectin in a single dose for the treatment of uncomplicated strongyloidiasis in adult patients, andCreation of a repository of serum and stool samples from adult patients (immunosuppressed and immunocompetent) with uncomplicated strongyloidiasis (samples before and after treatment with ivermectin) for later use in the evaluation of new diagnostic tools or biomarkers.

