### 2.6. Sample Size Calculation and Statistical Analysis

Assuming a response rate of 85% in the immunocompetent group, a 1-sided α value of 5%, a power of 80%, and a maximum of 10% non-evaluable subjects to show noninferiority at a margin of 14%, we estimated the sample size at 180 assessable subjects per group (90 patients in the IS group and 90 patients in the IC group). Inclusion will be performed competitively among all centers.

Categorical data will be presented as absolute numbers and proportions, and continuous variables will be expressed as means and standard deviations (when normal distribution is demonstrated using the Kolmogorov-Smirnov test) or as medians and interquartile ranges. The χ^2^ test or Fisher exact test, when appropriate, will be used to compare the distribution of categorical variables, and the Student’s *t* test or Mann–Whitney U test will be used for continuous variables. Results will be considered statistically significant if the *p* value is <0.05. SPSS software for Windows (Version 19.0; SPSS Inc, Chicago, IL, USA) will be used for statistical analyses. 

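### The noninferiority criterion in section 2.2 has its inequality reversed, contradicting the 14% margin in the same sentence and the sample size in section 2.6

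*Protocol article*

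**What the plan says.** Section 2.2 (Outcomes) of the protocol article sets the objective: "The primary outcome will be noninferiority of the cure rate of immunosuppressed patients compared to immunocompetent patients". It then names the margin, "We used a noninferiority margin of 14% to assess the primary outcome", and explains it in a parenthesis as "lower bound of the 1-sided 95% CI of the difference between cure rates in immunosuppressed versus immunocompetent patients was no more than –14" per cent. This is the only place in the article where the decision rule for the primary outcome is written out.

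Section 2.6 (Sample Size Calculation and Statistical Analysis) gives the design inputs: "Assuming a response rate of 85% in the immunocompetent group", "a 1-sided α value of 5" per cent, 80% power, and "a maximum of 10% non-evaluable subjects to show noninferiority at a margin of 14" per cent. The resulting group sizes are "90 patients in the IS group and 90 patients in the IC group".

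**The concern.** Cure is the favourable outcome, and the difference is expressed as IS versus IC, so a negative value means that IS patients do worse. To rule out a deficit of 14 points or more, the whole one-sided interval must lie above –14%, so its lower limit must be greater than –14%. The parenthesis in section 2.2 asks for a lower limit not exceeding –14%. The minus sign is printed, so on the number line this means –14% or anything further below. That condition describes a study that has failed to exclude a 14-point deficit.

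This sentence is the published prespecification of the primary success criterion. The Discussion links a favourable result to mass drug administration and to presumptive treatment of immunosuppressed migrants. A criterion with that use should not need the reader to reverse its inequality, least of all when the observed limit falls close to the margin.

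**Working it through.** **Inputs.** From section 2.6: IC cure 85%, one-sided α 5%, power 80%, 10% non-evaluable, 90 patients per group. From section 2.2: margin 14 points and a one-sided 95% lower limit. Two assumptions are needed. The IS cure rate is not stated and is taken as 85%, that is, no true difference. The interval method is not stated, and a Wald limit with unpooled variance is used. The sentence in 2.6 also attaches the figure 180 to each group; its parenthesis and the arithmetic below both point to 90 per group, 180 in all.

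**Step 1: reproduce the plan's sample size under the rule lower limit > –14%.**

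n per group = [0.85×0.15 + 0.85×0.15] × (1.645 + 0.842)² / 0.14²
= 0.255 × 6.183 / 0.0196 = 80.4, so 81 evaluable.

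Allowing for 10% non-evaluable: 81 / 0.90 = 90 per group, exactly the stated figure. Neither of two common alternatives matches: one-sided α of 2.5% gives 103 (115 after inflation), and a Farrington–Manning calculation gives 85 (95 after inflation).

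**Step 2: success probability under each rule, 81 evaluable per group, IC 85%.**

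SE = √[(0.85×0.15 + p(1–p)) / 81], where p is the true IS cure rate.
The literal rule is met when d – 1.645×SE ≤ –0.14, where d is the observed difference. Its probability is Φ{[–0.14 + 1.645×SE – (p – 0.85)] / SE}. The intended rule is the complement.

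| True IS cure | Literal rule (≤ –14%) | Intended rule (> –14%) |
|---|---|---|
| 85% | 19.8% | 80.2% |
| 80% | 55.3% | 44.7% |
| 71% (14 points worse) | 95.0% | 5.0% |
| 60% | 99.9% | 0.1% |

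Exact binomial enumeration with the Wald limit gives 19.8% and 94.8% for the literal rule at 85% and 71%. With a Newcombe limit the figures are 19.9% and 94.8%. The result therefore does not depend on the interval method.

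The intended rule returns the plan's own 80% power and 5% α. The literal rule turns them round. With 90 evaluable per group instead of 81, the literal rule is met 16.2% of the time at equal cure rates, so a larger study would be less likely to succeed when the groups are the same. No sample size calculation for 80% power at equal cure rates can rest on such a rule.

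**Step 3: two observed results, 81 per group.**

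- 85% versus 85%: SE = √(0.255/81) = 0.0561; lower limit = 0 – 1.645×0.0561 = –9.2%. Noninferiority is shown, yet the literal rule is not met.
- IS 60% versus IC 85%: SE = √(0.3675/81) = 0.0674; lower limit = –25.0% – 11.1% = –36.1%. Noninferiority clearly fails, yet the literal rule is met.

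**The case against.** The strongest reply is that no competent analyst would apply the literal rule. The parenthesis only explains a sentence that already fixes the margin, the scale, the interval and the limit to be used. Section 2.6 sizes the study for noninferiority at the same margin. The phrase can be read loosely as a deficit of at most 14 points, with the minus sign carried over by habit. This stands as far as intent goes: the right rule can be recovered from the document, and the literal error rates describe what the sentence says, not what is likely to happen. It does not make the sentence correct, and nothing else in the article restates the rule properly.

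Two stronger readings are tempting and are not supported.

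- A reader might infer that the design or the sample size is faulty. The exact reproduction of 90 per group under the intended rule speaks against that.
- A reader might infer that section 2.6 sets up a rival decision rule, because it says that the χ² or "Fisher exact test, when appropriate, will be used to compare the distribution of categorical variables", with significance at p < 0.05. A non-significant test of difference would indeed not show noninferiority. But 2.6 states this for categorical variables in general. It never assigns those tests to the primary outcome and never treats a non-significant p value as evidence of noninferiority. Section 2.2 assigns the primary outcome to a confidence limit, and further detail may sit in a full protocol or analysis plan that is not shown.

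**Conclusion.** The concern holds as an error in the written decision rule. Section 2.2 states the noninferiority criterion in the wrong direction, against its own margin and against the sample size in 2.6. Taken literally, with 81 evaluable per group and IC cure of 85%, the rule would be met about 95% of the time when IS cure is truly 71% and about 20% of the time when it is truly 85%, against about 5% and 80% for the intended rule. These figures assume a Wald limit; the literal-rule figures barely move with a Newcombe limit. The reproduction of 90 per group further assumes 85% cure in the IS group.

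The finding goes no further than the wording. Design, sample size, α and power are unaffected. The documents do not show that the study would in practice be declared a success on the reversed rule, or that the difference tests in 2.6 compete with the confidence limit.

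**What to change.** Replace the parenthesis in section 2.2 with: *noninferiority is concluded if the lower limit of the one-sided 95% CI for (cure rate IS – cure rate IC) is greater than –14%.* Any full protocol or analysis plan that repeats the criterion should be checked for the same reversal, and the correction should be dated before the primary outcome is analysed.

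The cost is one sentence. No change to sample size, data collection or conduct follows, since 81 evaluable and 90 enrolled per group already correspond to the corrected rule.

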## Abstract

Strongyloidiasis affects an estimated 600 million people worldwide, especially in tropical and subtropical areas. Single-dose ivermectin treatment has shown to be effective among immunocompetent patients with uncomplicated strongyloidiasis. Here, we present the protocol of the ImmunoStrong study, a prospective observational study aiming to evaluate the effectiveness and safety of a single-dose ivermectin for treatment of uncomplicated strongyloidiasis in immunosuppressed patients. The secondary objectives are to assess accuracy of molecular techniques for the follow-up of these patients and to determine the population pharmacokinetics of ivermectin. The information retrieved by this study will cover relevant information gaps in the strongyloidiasis management among immunosuppressed patients.

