### 2.1. Patient Eligibility

Inclusion criteria will include: Adult patients (≥18 years old) who sign the informed consent, diagnosis of strongyloidiasis either by direct parasitological methods (positive coproparasitological examination and/or agar plate culture) or by positivity of a serological technique (ELISA) with an optical density (OD) index greater than or equal to 2, and current residence in an area without evidence of active transmission of strongyloidiasis. The exclusion criteria will be as follows: Pregnancy or lactation, intolerance or allergy to ivermectin, renal failure (glomerular filtration rate equal to or less than 30 mL/min) or advanced liver disease (Child-Pugh B or C), coinfection by *Loa loa* (due to the risk of presenting encephalopathy when administering ivermectin), complicated strongyloidiasis (*S. stercoralis* hyperinfection syndrome or disseminated strongyloidiasis), planned trip to an area with evidence of active transmission of strongyloidiasis during the next 6 months (to avoid possible reinfections), and previous treatment with ivermectin (in the last year before inclusion).

Patients included in the IS group will be defined by presence of any of the following conditions at enrollment: Treatment with corticosteroids at a cumulative dose greater than or equal to 20 mg/day of prednisone (or equivalent) for at least 10 days, treatment with cytotoxics drugs or antimetabolites, bone marrow or solid organ transplantation, biological drugs, active solid or hematological neoplasia, HIV infection with CD4 lymphocyte count below 200 cells/mm^3^. On the other hand, patients included in the IC group must not have any of the previous conditions (and no HIV infection regardless of the CD4 lymphocyte count).

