The strongyloidiasis diagnosis and follow-up in the ImmunoStrong study is mainly based on serological techniques, which is closer to real-life conditions. Some concerns could arise regarding the sensitivity of serological techniques in immunosuppressed patients, and this fact could affect the patients’ recruitment of the IS group. Regarding specificity issues of the serological techniques, it has been suggested that increasing the cut-off value for positive serology may increase the specificity of the serological test in the diagnosis of confirmed strongyloidiasis [19]. For this reason, patients included in the ImmunoStrong study must have an OD index equal to or greater than 2 in the ELISA test at the time of diagnosis in the absence of larvae detection in parasitological techniques. 

Novel molecular-based diagnostic techniques for strongyloidiasis diagnosis have been developed in the last decades to achieve the highest sensitivity and specificity. A recent meta-analysis, which included 14 studies, evaluated the accuracy of molecular biology techniques for the diagnosis of *S. stercoralis* infection, showing very high specificity of the PCR technique. However, sensitivity showed unsatisfactory results regardless of the reference test used [20]. Moreover, among the 14 included studies, only 1 was performed in immunosuppressed patients, showing scarce benefits of PCR techniques compared with classical parasitological techniques in patients with oncologic diseases [21]. This gap of information will also be covered by the ImmunoStrong study, which will compare the PCR technique with classical parasitological techniques and serology for the strongyloidiasis diagnosis and follow-up after treatment, both in immunocompetent and immunosuppressed patients.

Finally, the present study will perform an ivermectin population pharmacokinetics among the included patients. The information of this sub-study among immunosuppressed patients could be crucial, since this population is usually under a broad range of treatments that could affect the ivermectin concentrations in blood, subsequently affecting the potential efficacy of the single-dose strategy. 

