Concluding, the ImmunoStrong study will focus on the strongyloidiasis treatment among immunosuppressed patients, aiming to find an effective and easier method to implement the treatment scheme based on ivermectin. Information about the accuracy of the PCR technique for the diagnosis and follow-up of these patients and the ivermectin population pharmacokinetics will also fill information gaps in this kind of population.

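### The PCR follow-up sub-study compares two overall proportions, which cannot measure the accuracy it sets out to assess

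*Protocol article*

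**What the plan says.** The Abstract lists among the secondary objectives to "assess accuracy of molecular techniques for the follow-up of these patients". The closing paragraph of the Discussion again promises "Information about the accuracy of the PCR technique for the diagnosis and follow-up of these patients".

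Section 2.2 lists PCR as the first of three prespecified sub-studies and describes it as an evaluation of usefulness "in the follow-up after treatment of uncomplicated strongyloidiasis in adult patients". The measure in parentheses is the proportion of patients with negative "PCR after treatment compared to proportion of patients that fulfill the cure criteria". It names no visit for the PCR result, no restriction by baseline PCR and no patient-level comparison.

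Three other places bear on this:
- Section 2.1 admits patients with positive stool tests "or by positivity of a serological technique (ELISA) with an optical density (OD) index greater than or equal to 2".
- Table 1 plans PCR at screening, month 3 and month 6. Its footnote c limits repeat stool examination and culture to patients positive at baseline; the PCR row carries no such footnote.
- The Discussion says of PCR in an earlier meta-analysis that "sensitivity showed unsatisfactory results regardless of the reference test used", and calls its specificity very high. It gives no figures.

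**The concern.** Accuracy is a property of the joint classification: among patients not cured, how many does PCR flag, and among those cured, how many does it clear? The stated measure uses only the two totals, so a perfect test and a useless one can give the same result.

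A second problem adds to this. A patient who is PCR-negative before treatment cannot show PCR clearance. If that patient stays negative, the result counts toward the PCR-negative proportion all the same. Because entry on serology alone is allowed and PCR is described as insensitive, such patients may be numerous.

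The Discussion presents PCR follow-up in immunosuppressed (IS) patients as an evidence gap that this study will cover. A PCR-negative proportion close to the cure rate could be read as support for PCR as a test of cure when the data show nothing of the kind.

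**Working it through.** **Number of evaluable patients.** Inputs from section 2.6: response 85%, margin 14 percentage points, one-sided alpha 5%, power 80%, 10% non-evaluable.

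n per group = 2 × 0.85 × 0.15 × (1.6449 + 0.8416)² / 0.14² = 80.4, rounded up to 81. Then 81 / 0.90 = 90 per group, which reproduces the plan's figure. The total is 180, of whom 2 × 81 = 162 are evaluable. The PCR sub-study has no sample size of its own, so 162 is used for illustration.

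**Same totals, different accuracy.** Apply the 85% rate to both groups: 0.85 × 162 = 137.7, so take 138 cured and 24 not cured. Suppose that 138 are also PCR-negative and 24 PCR-positive after treatment. The stated comparison is then 85.2% against 85.2%, a difference of 0.

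Let d be the number both non-cured and PCR-positive. The totals allow any d from 0 to 24.
- Discordant patients = 2 × (24 − d)
- Agreement = 1 − discordant / 162
- Chance agreement = (138² + 24²) / 162² = 0.748
- Kappa = (agreement − 0.748) / (1 − 0.748), computed unrounded
- Sensitivity for non-cure = d / 24; specificity = (138 − (24 − d)) / 138

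| d | Discordant | Agreement | Kappa | Sensitivity | Specificity | Difference in proportions |
|---|---|---|---|---|---|---|
| 24 | 0 | 100% | 1.00 | 100% | 100% | 0 |
| 4 | 40 | 75.3% | 0.02 | 16.7% | 85.5% | 0 |
| 0 | 48 | 70.4% | -0.17 | 0% | 82.6% | 0 |

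The row d = 4 is close to pure chance (24 × 24 / 162 = 3.6). This result needs no assumption about baseline PCR positivity. McNemar's statistic is also 0 in all three rows, because the discordant patients split equally in each.

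**Effect of patients never PCR-positive.** Let b be the proportion PCR-positive at baseline and c the proportion of those who clear. If no baseline-negative patient converts, the PCR-negative proportion after treatment is 1 − b(1 − c). The documents give no value for b, so the range below is assumed.

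| b | PCR-negative after, c = 0 | PCR-negative after, c = 85% | Share of those negatives already negative at baseline (c = 85%) | Baseline-positive patients of 162 |
|---|---|---|---|---|
| 20% | 80% | 97% | 82% | 32 |
| 40% | 60% | 94% | 64% | 65 |
| 60% | 40% | 91% | 44% | 97 |
| 80% | 20% | 88% | 23% | 130 |

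At b = 15% with no clearance and no conversion, 1 − 0.15 = 85% would be PCR-negative, which equals the cure rate assumed for the immunocompetent (IC) group.

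**The case against.** The strongest reply is that one parenthesis in a condensed article is not the whole analysis. The Discussion says that PCR will be compared with parasitology and serology, at diagnosis and follow-up, in both groups, and the full protocol or analysis plan may specify a cross-tabulation. That is possible. But the Discussion names no other measure, and section 2.2 does state one, as prespecified, that does not match the aim. This is a measure badly fixed, not a detail left out.

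Several stronger readings are tempting but not supported:
- **That all patients, whatever their baseline PCR, form the denominator.** Section 2.2 does not say so. It is an inference from the lack of any restriction, and footnote c governs which tests are repeated, not the analysis set.
- **That baseline PCR-negative patients carry no information.** An insensitive test can miss an infection at baseline and detect it later. Such a conversion is informative about failure. What holds is that these patients cannot show clearance.
- **That they are the majority.** The documents give no figure.
- **That an 85% PCR-negative rate produced by partial clearance in a minority proves disagreement with cure.** The 15% still positive could be exactly the 15% not cured. Only the cross-tabulations above show what equal totals can hide.
- **That the plan prescribes an invalid test here.** The sentence in section 2.6 that the χ² or "Fisher exact test, when appropriate, will be used to compare the distribution of categorical variables" is general and is not assigned to this sub-study. Tests for independent samples would ignore the pairing if used here, but the document does not say that they will be.

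**Conclusion.** The point holds. The measure in section 2.2 does not identify the accuracy named as the aim in the Abstract and Discussion. At 162 evaluable patients and equal totals of 138, it is compatible with agreement from 70.4% to 100% and with PCR detecting anything from none to all of the 24 non-cured patients. That conclusion rests only on the plan's own rate and sample size, with the 85% applied to both groups.

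The dilution by patients never PCR-positive is a real but unquantified addition: its size depends on baseline positivity, which is not given, and on how many patients convert from negative to positive.

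The flaw should be corrected but is limited to a sub-study. The primary outcome, its sample size and the data collection are untouched.

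**What to change.** Replace the comparison of proportions in section 2.2 with the following:
- A within-patient cross-tabulation of month-6 PCR against month-6 cure status, with month-3 PCR as an earlier marker against the same status.
- Sensitivity and specificity of PCR for non-cure, and kappa, with 95% confidence intervals, overall and by IS and IC group.
- PCR clearance among patients PCR-positive at baseline, with that denominator stated.
- Baseline PCR positivity and negative-to-positive conversions, each reported separately.

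McNemar's test is not a substitute. It respects the pairing but tests only whether the two totals are equal.

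The cost is wording, since PCR is already planned at screening, month 3 and month 6. The downside is precision. About 24 non-cured patients are expected, or about 12 per group if evenly split; a sensitivity of 6 of 12 would have an exact 95% interval of about 21% to 79%. The clearance denominator also shrinks, to between about 32 and 130 of 162 over the assumed range. Results by group should therefore be presented as descriptive.
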